#### Cardiac magnetic resonance imaging

Ejection fraction, regional wall motion abnormalities, myocardial fibrosis, oedema and presence of infarction will be determined as previously described [11, 13, 29]. Briefly, epicardial and endocardial contours will be drawn around diastolic phase cines, and endocardial contours around systolic phase cines to calculate cardiac volumes and myocardial mass. The myocardium will be separated into 16 segments of the American Heart Association 17-segment model excluding the apex [28]. T1 values,T2 values, extra cellular volume and the presence of late gadolinium enhancement will be generated for each segment using dedicated software. T1 values will indicate fibrosis, T2 values oedema and gadolinium enhancement the presence of infarction as well as fibrosis depending on distribution [11, 13, 20].

## Primary objectives

We have four primary objectives:Identify the proportion of patients with biochemical evidence of myocardial injury or strain with the presence of elevated cardiac troponin.Identify significant atherosclerotic disease potentially causing cardiac injury with the presence of obstructive coronary artery disease on CTCA (> 50%).Identify myocardial disease using CMR by determining ejection fraction, presence of myocardial infarction (sub-endocarditis gadolinium enhancement), myocarditis (mid-wall/epicardial gadolinium enhancement) or myocardial oedema (elevated T1 values and T2 values)Identify vascular inflammation by 18F-FDG-PET/CT by quantifying increased FDG uptake in aorta. Determining the presence of different patterns of FDG uptake in myocardium will be a secondary exploratory outcome.

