## Methods/design

This is a single-centre exploratory observational study involving participants diagnosed with COVID-19 receiving care at the Aga Khan University Hospital in Nairobi, Kenya. We aim to recruit around 50 patients with COVID-19 infection with 20 to 30 patients undergoing cardiac imaging. If feasible we will aim to image 15–20 with plasma troponin levels, using a high-sensitivity assay, above the 99th centile upper reference limit (URL) and 5–10 patients with troponin levels within the normal reference range. We will additionally identify a control population of individuals where COVID-19 is suspected but excluded following testing. We will attempt to match controls by age and sex to the COVID-19 positive population. All patients not requiring non-invasive and invasive ventilation will be eligible for recruitment.

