### Selection criteria

Inclusion criteria for patients diagnosed with COVID-19 include those over the age of 18 years, testing positive on PCR testing and ideally within 2 weeks of a positive test. Patients will be excluded based on the following conditions: (1) prior diagnosis of myocardial infarction, coronary revascularisation or cardiac surgery; (2) requiring invasive or non-invasive ventilation; (3) inability to undergo CT or CMR scanning; (4) severe renal failure (estimated glomerular filtration rate < 30 mL/min); (5) Major allergy to iodinated contrast media/gadolinium; (6) pregnancy or breast feeding; (7) inability to give informed consent; (8) contraindication to imaging example metal fragments in the eye. Similarly exclusion criteria will apply to patients over the age of 18 years chosen as controls and testing negative for COVID-19.

We will also explore stratification by clinical parameters of COVID-19 severity. As such we will also provide baseline characteritics and imaging parameters by clinical requirement of oxygen supplementation.

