#### Cardiac magnetic resonance

Standard CMR images will be acquired as previous [17–19]. In brief, standard pilot images and cardiac views will be obtained using breath-held acquisitions. Sequences will be as follows: (1) HASTE/White blood axial; (2) cines 2, 3 and 4 chamber; (3) T1 map short axis basal and mid-ventricular short axis slices, with additional long axis images if possible; (4) T2 map short axis basal and mid-ventricular short axis slices, with additional long axis images if possible; (5) post gadolinium contrast PSIR short axis cine stack, 2, 3 and 4 chamber; (6) post contrast T1 map short axis basal and mid-ventricular short axis slices; (7) aortic flow map.

Gadolinium-based contrast agent will be intravenously administered. Myocardial infarction and fibrosis will be identified by the presence of hyperenhancement in the myocardium in late enhancement images, acquired using a T1-inversion sequence with inversion time optimised on a patient-by-patient basis [20]. Multiple slices will be acquired in the short axis view with inversion time further optimised for each slice. Two- and 4-chamber late enhancement views will also be acquired to verify presence or absence of late enhancement. Late enhancement images will be acquired approximately 5–12 min after gadolinium infusion. T1 characteristics, extra cellular volume as well as the presence of cardiac oedema by T2-maps will be assessed [11, 13, 21].

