## Sample size calculation and statistics

Based on published literature we based our sample size calculation on the assumption that 1 in 4 of hospitalised COVID-19 patients will have elevated cardiac troponin [3]. In sample size calculations, we estimated that with 50 patients, we would be able to estimate the confidence interval for a prevalence of 25% with lower and upper intervals of 14.1% and 37.4% respectively, and that we would have 80% power for an alpha of 0·05 to test the null hypothesis that the prevalence was < 10%. This is an exploratory observational cross-sectional study to investigate the potential cardiac mechanisms in patients with COVID-19. As such we have not performed any formal power calculations based on imaging parameters.

Baseline clinical and imaging data will will be expressed as the mean ± standard deviation (SD) for parametric data and median (interquatile range) for non-parametric data. Categorical data will be presented as proportions. We will conduct hypothesis testing based on imaging parameters comparing (a) controls and patients and (b) within patients, those stratified by troponin concentrations. For within patient analysis we will attempt to compare individuals stratified above and below the 99th centile for cardiac troponin concentration. If the number of patients above the 99th centile for cardiac troponin are small, we will group patients by equal strata of cardiac troponin value. We will also explore stratification by clinical parameters of COVID-19 severity. As such we will provide also provide baseline characteritics and imaging parameters by clinical requirement of oxygen supplementation. *P* value of less than 0.05 will indicate statistical significance.

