## Discussion

In order to understand cardiac complications secondary to COVID-19, this study aims to utilise multimodality cardiac imaging to identify any morphological and functional cardiovascular changes associated with infection. To date, whilst data has shown that myocardial injury is prevalent in patients with COVID-19, cardiac imaging has either been limited to case reports and small case series, performed after recovery using single modalities or using study designs highly susceptible to selection/reporting [8–10].

To our knowledge, our study represents the first multi-modality cardiac imaging study, with each technique attempting to elucidate specific pathophysiological processes. CTCA will examine the presence of coronary disease associated directly or indirectly with elevated cardiac troponin concentrations, and its absence would imply Type 2 myocardial infarction in the correct context. CMR will evaluate cardiac function and dysfunction including structural evidence of heart failure resulting from either ischaemic or non-ischaemic cardiomyopathy (e.g. stress cardiomyopathy). It will also identify myocardial infarction or fibrosis caused by myocarditis. 18F-FDG-PET/CT can assess for myocardial and vascular inflammation that would delineate if myocardial oedema (seen on CMR) is caused by direct cardiac injury or as part of a generalised inflammatory process.

Identification of each pathophysiological process will inform future studies in evaluating optimal choices of therapeutic agents; (1) anti-platelet and anti-coagulation agents for atherosclerotic disease or thrombotic occlusions; (2) Blood pressure and oxygen support in the presence of type 2 myocardial infarction; (3) anti-viral or anti-inflammatory strategies for a primary myocarditic processes; (4) early and long term cardioprotective therapy for myocardial dysfunction.

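### The primary CMR objective labels mid-wall or epicardial late enhancement as myocarditis with no sign of acute disease required, so it does not separate acute myocarditis from older non-ischaemic fibrosis

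*Protocol article*

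**What the plan says.** - **Primary objectives**, third objective: CMR is to identify myocardial disease through ejection fraction, infarction (subendocardial enhancement), "myocarditis (mid-wall/epicardial gadolinium enhancement", "or myocardial oedema (elevated T1 values and T2 values". The last two are joined by *or*, so oedema is not a condition for the myocarditis label.
- **Image acquisition, Cardiac magnetic resonance**: "Myocardial infarction and fibrosis will be identified by the presence of hyperenhancement in the myocardium in late enhancement images". Myocarditis is not named.
- **Image analysis, Cardiac magnetic resonance imaging**: T1 is read as fibrosis, T2 as oedema, and "gadolinium enhancement the presence of infarction as well as fibrosis depending on distribution". T1, T2, extracellular volume and late enhancement are generated for each of 16 segments.
- **Discussion**, on CMR: "It will also identify myocardial infarction or fibrosis caused by myocarditis".
- **Selection criteria**: the cardiac history that excludes a patient is "prior diagnosis of myocardial infarction, coronary revascularisation or cardiac surgery". Prior myocarditis, cardiomyopathy and heart failure are not listed.
- **Methods/design**: "We will additionally identify a control population of individuals where COVID-19 is suspected but excluded following testing". Age and sex matching will be attempted.
- **Sample size calculation and statistics**: "We will conduct hypothesis testing based on imaging parameters comparing (a) controls and patients", and also patients by troponin level. No power calculation was made for imaging parameters.

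**The concern.** Late enhancement is a tissue finding without a date. The acquisition and analysis sections treat it that way, as infarction or fibrosis. The primary objective turns the non-infarct pattern into an inflammatory diagnosis and asks for no evidence that the process is current.

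The stated aim is to identify cardiac mechanisms related to COVID-19, and the Discussion ties a primary myocarditic process to a particular class of therapies for future study. If the myocarditis category can include fibrosis that predates the infection, its frequency does not answer the mechanism question. The infarction category has the same gap: the exclusion requires a prior diagnosis, so an undiagnosed old infarct would count.

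**Working it through.** The protocol gives no prevalence, precision or power for any CMR finding, so there is no figure to reproduce. The check is a reading of the rule, followed by an illustration.

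**Applying the rule.** Take a patient with mid-wall enhancement that predates the infection and with normal T2.
1. Selection criteria: the patient enters, because only prior infarction, revascularisation and cardiac surgery exclude on cardiac history.
2. Acquisition and analysis sections: the enhancement is read as fibrosis, and T2 shows no oedema.
3. Primary objectives: the pattern is mid-wall, so the patient is classed as myocarditis. Normal T2 changes nothing, because oedema is a separate item.
4. Nothing later revises the label. No earlier CMR is described for comparison. CMR analysts are blinded to blood results and other modalities, and the centres do not discuss scans. Myocardial FDG patterns are a secondary exploratory outcome and are not part of the CMR definition.

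**Illustration.** Let *b* be the share of imaged patients with pre-existing non-ischaemic enhancement and *t* the share with new myocarditis. Both are assumptions with no value in the documents. The number imaged, *n*, is 20 to 30 (Methods/design).

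- Expected pre-existing scars that meet the definition: *n·b*
- Chance of at least one: 1 − (1 − *b*)^*n*
- Observed proportion, if the two are independent: 1 − (1 − *b*)(1 − *t*)
- Share of positives that are scar only: *b*(1 − *t*) / [1 − (1 − *b*)(1 − *t*)]

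| *b* (assumed) | Expected, n = 20 / 30 | At least one, n = 20 / 30 | Scar-only share, *t* = 5% / 10% / 20% |
|---|---|---|---|
| 2% | 0.4 / 0.6 | 33% / 45% | 28% / 15% / 7% |
| 5% | 1.0 / 1.5 | 64% / 79% | 49% / 31% / 17% |
| 10% | 2.0 / 3.0 | 88% / 96% | 66% / 47% / 29% |
| 20% | 4.0 / 6.0 | 99% / over 99% | 79% / 64% / 44% |

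Example: *b* = 10%, *t* = 10% gives 1 − 0.90 × 0.90 = 19% observed, of which 0.10 × 0.90 / 0.19 = 47% is scar only. Across the grid the share runs from 7% to 79%, so the assumptions decide the answer. What does not depend on them is the weight of one patient: 1/30 = 3.3 points to 1/20 = 5 points.

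**What the controls can do.** If controls have the same *b* and no acute myocarditis, the patient-minus-control difference is [1 − (1 − *b*)(1 − *t*)] − *b* = *t*(1 − *b*). In the example this is 19% − 10% = 9%, close to *t*. The patient proportion itself stays at 19%. The troponin comparison is made within patients and does not use the controls.

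**The case against.** The other side has substance.

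- **No flat contradiction.** A reader might infer that the sections contradict each other outright. They do not. The analysis section says the reading depends on distribution, the primary objective uses distribution, and the Discussion links fibrosis to myocarditis as its cause. One is a tissue sign and the other an inferred cause. This stands. What remains is that the cause is assumed and its timing is not addressed.
- **No category of COVID-19 myocarditis.** A reader might also infer that old scar is counted as myocarditis due to COVID-19. The protocol uses no such term. It speaks of identifying myocardial disease, calls the study exploratory and cross-sectional, and plans a COVID-negative comparison. This stands. The controls address attribution at group level, but the comparison is unpowered, matching is only attempted, and they leave the patient proportion and the troponin comparison as they were.
- **Evidence on acuity is already collected.** T2 per segment, oedema as its own item, and segmental FDG uptake intended for comparison with CMR are all in the plan. This is true, and it makes the fix cheap. None of it enters the definition, and the definition is stated in this article, not left to another document.
- **Requiring raised T2 could err the other way.** T1 and T2 maps cover basal and mid-ventricular slices, with long-axis maps only if possible. CMR may take place beyond two weeks, and the limitations note that anti-inflammatory drugs may dampen the signal. This stands, and it rules out making raised T2 mandatory.

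**Conclusion.** The point holds as a weakness of definition. As written, the primary CMR objective does not separate acute myocarditis from older non-ischaemic fibrosis, and nothing elsewhere in the article closes that gap for the patient proportion or for the comparison by troponin.

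Its size is unknown. It would be tempting to say that about half of the reported myocarditis would be false, but that follows only from assuming equal rates of old scar and new disease. It would also be tempting to say that the rule creates a false link between troponin and myocarditis. That needs prior non-ischaemic disease to go with raised troponin. The Background connects cardiovascular comorbidity with more severe COVID-19 but gives no figure for this, so it is a possibility and not a finding.

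The conclusion rests on two assumptions: that some imaged patients may have non-ischaemic enhancement predating the infection, which the exclusions allow, and that raised T2, which the protocol reads as oedema, supports a current process. No stated figure in the protocol changes.

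**What to change.** 1. In Primary objectives, replace the myocarditis label with *non-ischaemic (mid-wall/epicardial) late enhancement*.
2. Report that sign, and subendocardial enhancement, in three groups from the per-segment data: raised T2 in the corresponding mapped segments (supports acute injury), normal T2 (age undetermined), and not assessable because the segment was not mapped.
3. Show alongside each group the FDG uptake in the same segments and the time from positive test to CMR. These can be joined after the blinded reads, so blinding is kept.
4. Give the same split in controls.
5. Do not make raised T2 an absolute requirement.
6. Use the same terms in the CMR acquisition section, the CMR analysis section and Primary objectives. T1 needs the same attention: the analysis section reads it as fibrosis, while the objective uses raised T1 together with T2 for oedema.

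The cost is wording and one derived variable, with no extra scan or reader. Fewer patients will carry a firm label of acute myocarditis, and some lesions will fall into the undetermined or not-assessable groups because of limited map coverage, late scans or anti-inflammatory treatment.

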## Sample size calculation and statistics

Based on published literature we based our sample size calculation on the assumption that 1 in 4 of hospitalised COVID-19 patients will have elevated cardiac troponin [3]. In sample size calculations, we estimated that with 50 patients, we would be able to estimate the confidence interval for a prevalence of 25% with lower and upper intervals of 14.1% and 37.4% respectively, and that we would have 80% power for an alpha of 0·05 to test the null hypothesis that the prevalence was < 10%. This is an exploratory observational cross-sectional study to investigate the potential cardiac mechanisms in patients with COVID-19. As such we have not performed any formal power calculations based on imaging parameters.

Baseline clinical and imaging data will will be expressed as the mean ± standard deviation (SD) for parametric data and median (interquatile range) for non-parametric data. Categorical data will be presented as proportions. We will conduct hypothesis testing based on imaging parameters comparing (a) controls and patients and (b) within patients, those stratified by troponin concentrations. For within patient analysis we will attempt to compare individuals stratified above and below the 99th centile for cardiac troponin concentration. If the number of patients above the 99th centile for cardiac troponin are small, we will group patients by equal strata of cardiac troponin value. We will also explore stratification by clinical parameters of COVID-19 severity. As such we will provide also provide baseline characteritics and imaging parameters by clinical requirement of oxygen supplementation. *P* value of less than 0.05 will indicate statistical significance.

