**Methods:**

This is a single-centre exploratory observational study aiming to recruit 50 patients with COVID-19 infection who will undergo cardiac biomarker sampling. Of these, 30 patients will undergo combined CTCA and 18F-FDG-PET/CT, followed by CMR. Prevalence of obstructive and non-obstructive atherosclerotic coronary disease will be assessed using CTCA. CMR will be used to identify and characterise myocardial disease including presence of cardiac dysfunction, myocardial fibrosis, myocardial oedema and myocardial infarction. 18F-FDG-PET/CT will identify vascular and cardiac inflammation. Primary endpoint will be the presence of cardiovascular pathology and the association with troponin levels.

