### Image acquisition

At initial recruitment, patients will undergo blood sampling for high-sensitivity cardiac troponin, N-terminal pro B-type natriuretic peptide and high-sensitivity C Reactive protein. A subset of patients will be selected for multimodality cardiovascular imaging. These participants will undergo two visits for a combined CTCA and 18F-FDG-PET/CT as soon as possible, followed by a CMR on another visit. All CTCA and 18F-FDG-PET/CT will be performed within 2 weeks of presentation to maximise sensitivity of the scan. All efforts will be made to ensure CMR scans are also performed within 2 week, however scanning beyond this point will be performed if it is logistically impossible to perform the scan within this window.

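### The imaging subset is enriched, if feasible, for raised troponin, yet it is pooled for the comparison with controls and for the CTCA prevalence, so those figures can be shifted by selection

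*Protocol article*

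**What the plan says.** All places are in the protocol article.

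- **Who is imaged.** Methods/design: "We aim to recruit around 50 patients with COVID-19 infection with 20 to 30 patients undergoing cardiac imaging". The composition is a conditional target: "If feasible we will aim to image 15–20 with plasma troponin levels, using a high-sensitivity assay, above the 99th centile upper reference limit (URL", with "5–10 patients with troponin levels within the normal reference range". Image acquisition confirms that imaging is not for everyone: "A subset of patients will be selected for multimodality cardiovascular imaging". The same section has troponin measured at recruitment.
- **The source population.** Sample size calculation and statistics rests on "the assumption that 1 in 4 of hospitalised COVID-19 patients will have elevated cardiac troponin".
- **Controls.** These are people in whom COVID-19 was suspected and then excluded. Methods/design: "We will attempt to match controls by age and sex to the COVID-19 positive population". Their troponin mix is not stated.
- **Analysis.** Sample size calculation and statistics: "We will conduct hypothesis testing based on imaging parameters comparing (a) controls and patients and (b) within patients, those stratified by troponin concentrations". Categorical data are summarised as proportions, and P below 0.05 counts as significant. Troponin strata appear in (b) only. If few patients exceed the 99th centile, the section groups patients by equal strata of troponin instead.
- **Target of estimation.** Abstract, Methods: "Prevalence of obstructive and non-obstructive atherosclerotic coronary disease will be assessed using CTCA". The same paragraph makes the association of cardiovascular pathology with troponin part of the primary endpoint.

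**The concern.** The imaged patients are chosen partly on a variable that the study itself expects to be linked to the imaging findings. Choosing them this way is sound for comparing high- with low-troponin patients. It is not sound for a pooled proportion or mean meant to describe patients with COVID-19, because the pooled figure then depends on the quota as well as on the disease.

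Two results are exposed: the overall proportions with an imaging finding (explicitly a prevalence for coronary disease), and comparison (a), the one planned test of patients against controls. A reader could credit to COVID-19 a difference that comes from how patients were picked for scanning. The limitations in the Discussion do not mention the enrichment, although the Discussion faults earlier studies for susceptibility to selection.

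**Working it through.** **1. The plan's own figure.** The only power statement is 80% for n = 50, prevalence 25% against a null of 10%, alpha 0.05. The two-sided arcsine formula gives 2 × (asin√0.25 − asin√0.10) × √50 − 1.96 = 2.855 − 1.96 = 0.895, so power is 81.4%. The figure reproduces. It concerns the troponin proportion in all recruits; no figure is given for imaging.

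**2. Raised-troponin share f of the imaged set.**
- At target: 15/25 = 60%, 20/30 = 67%, 15/20 = 75%, 20/25 = 80%. Against 25%, that is 2.4 to 3.2 times over-represented.
- Feasibility: 0.25 × 50 = 12.5 raised-troponin patients are expected. By the binomial, P(15 or more) = 25% and P(20 or more) = 1.4%.
- With 12 raised among 20–30 imaged: 12/20 = 60% down to 12/30 = 40%. The lower end needs 18 normal-troponin patients, more than the 5–10 targeted.

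**3. Bias formulas.** Let pH and pL be the rates of a finding in raised- and normal-troponin patients, and c the raised share in controls.
- Pooled proportion against the recruited population: (f − 0.25) × (pH − pL).
- Difference from controls with no COVID-19 effect: (f − c) × (pH − pL).

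Both are zero if findings are unrelated to troponin. The second is also zero if c = f.

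**4. Illustration.** The article gives no imaging rates, number of controls or value of c, so all of these are assumptions: pH = 60%, pL = 20%, c = 25%, 20 controls. The proportion in unselected recruits is 0.25 × 0.60 + 0.75 × 0.20 = 30%. The rejection column is simulated: a two-sided 5% t-test on a continuous parameter that differs by 1 SD between troponin groups, with no COVID-19 effect.

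| Raised / normal imaged | f | Pooled proportion | Excess over 30% | Rejection |
|---|---|---|---|---|
| 20 / 5 | 80% | 52% | 22 points | about 37% |
| 15 / 5 | 75% | 50% | 20 points | about 28% |
| 20 / 10 | 67% | 46.7% | 16.7 points | about 24% |
| 15 / 10 | 60% | 44% | 14 points | about 16% |
| 12 / 8 | 60% | 44% | 14 points | about 15% |
| 12 / 18 | 40% | 36% | 6 points | about 6% |

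With a 0.5 SD difference, rejection at the four target splits is about 8–14%.

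**5. Sensitivity to the assumptions.**
- Rates of 40% and 10%: the pooled proportion is 28–34% at the target splits, against 0.25 × 0.40 + 0.75 × 0.10 = 17.5%.
- Rates of 30% and 10%: 22–26%, against 15%.
- Fisher's test at 0.05 with rates of 40% and 10%, 30 patients and 30 controls: with c = 25%, rejection is about 10%, 13% and 22% for f = 60%, 67% and 80%. With c = 5% it is about 25%, 31% and 44%. The result depends strongly on the controls' unknown mix.

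**6. Cost of weighting back to 25%.** The Kish effective sample size is 1 / [h × (0.25/h)² + l × (0.75/l)²] for h raised and l normal patients: 8.6 for 15/5, 8.6 for 20/5, 16.6 for 15/10 and 16.8 for 20/10. For 12/18 it is 27.4.

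**The case against.** - **The quota may not be met.** This stands. The target is conditional, 50 recruits reach 15 raised-troponin patients only one time in four on the protocol's own assumption, and the statistics section foresees a shortfall. A reader might infer that the imaged set will be 60–80% raised; the article supports that only as an aim. With 12 raised among 30 the excess is 6 points and the test hardly departs from 5%. The bias shrinks but keeps its direction.
- **A false difference from controls is not inevitable.** This also stands. A reader might infer that (a) must favour a COVID-19 effect. That needs raised troponin to be rarer in controls than in the imaged patients, and the controls' mix is unknown.
- **Most imaging objectives are not prevalences.** Correct. A reader might infer that all three imaging objectives are overstated prevalences. Primary objectives 2–4 speak of identifying disease, objective 4 quantifies aortic uptake, and within the planned analyses the abstract uses prevalence for coronary disease only. The point therefore reaches CTCA directly, and other findings only where pooled figures are reported as describing patients with COVID-19.
- **Stratified analysis is already planned.** In part. Comparison (b) uses troponin strata and is well served by enrichment, but it does not correct the pooled (a).
- **A condensed article leaves detail to an analysis plan.** This is fair for covariate adjustment: the absence of age and sex from the comparison, or of a rule for choosing patients within a stratum, is silence and is not held against the plan. The pooled contrast and plain proportions, however, are stated in the text.
- **The study is exploratory.** That lowers the severity. It does not make an unweighted proportion from a quota sample a prevalence, and significance testing is planned.

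**Conclusion.** The point holds in a limited form. Read as written, the plan uses a troponin-enriched imaging set, unweighted, for the CTCA prevalence and for the comparison with controls. If imaging findings are associated with troponin, which the primary endpoint presupposes, pooled COVID-19 proportions are too high for the recruited population. Comparison (a) may then differ from zero without a COVID-19 effect if controls have less raised troponin.

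Under the stated assumptions the excess is about 6–22 points and the 5% t-test rejects about 6–37% of the time, depending on the split achieved. The larger values need the full quota, which is unlikely from 50 recruits. Comparison (b) is not affected. Nor is the troponin proportion in all 50, provided recruitment itself is not steered by troponin.

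Severity: should be fixed before analysis. The documents do not support treating it as fatal to an exploratory study.

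**What to change.** In Sample size calculation and statistics:

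1. Report imaging proportions and means, and comparison (a), separately for raised- and normal-troponin patients.
2. Weight any overall COVID-19 figure to the troponin distribution of all recruits. Troponin is measured in everyone at recruitment, so the fraction imaged in each stratum is known. If the fallback to equal troponin strata is used, weight over those strata.
3. Do not call an unweighted proportion from the imaged subset a prevalence; change the abstract to match.

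In the Discussion, list the enrichment as a limitation, and say that the reading of (a) depends on the controls' troponin mix.

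This needs no extra scans and no change in who is imaged. The cost is precision: at the planned splits the weighted overall estimate carries the information of about 9–17 patients from the 20–30 imaged, and the normal-troponin stratum may hold only 5–10 people. Intervals will be wide and should be shown.

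### The equal-strata fallback for troponin is undefined, can place normal-troponin patients in the high group, and has less power than analysing troponin as a continuous variable

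*Protocol article*

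**What the plan says.** The protocol article's section on sample size and statistics announces hypothesis tests on imaging parameters at P below 0.05, between controls and patients and, within patients, by troponin. On the second it says: "For within patient analysis we will attempt to compare individuals stratified above and below the 99th centile for cardiac troponin concentration". It then gives the fallback: "If the number of patients above the 99th centile for cardiac troponin are small, we will group patients by equal strata". The sentence ends by saying that the strata are of troponin value. It does not say how few patients count as small, how many strata there will be, or whether equal means equal numbers of patients or equal width on the troponin scale. No analysis with troponin as a continuous variable is described.

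The Methods/design section sets the numbers: "We aim to recruit around 50 patients with COVID-19 infection with 20 to 30 patients undergoing cardiac imaging", and "If feasible we will aim to image 15–20 with plasma troponin levels, using a high-sensitivity assay, above the 99th centile" reference limit, together with 5–10 patients in the normal range. The sample size rests on the assumption that "1 in 4 of hospitalised COVID-19 patients will have elevated cardiac troponin". The abstract gives the comparison weight: "Primary endpoint will be the presence of cardiovascular pathology and the association with troponin levels".

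**The concern.** The 99th centile is the plan's own dividing line between raised and normal troponin, and raised troponin is its own marker of myocardial injury (Primary objectives, first item). Above against below that line is therefore a contrast of injury with no injury. Strata of equal size cut the sample wherever the ranks happen to fall. When few patients are raised, which is the only case in which the fallback applies, the cut falls inside the normal range and the upper group is partly made up of uninjured patients. A difference found, or not found, between such groups does not answer the question that the abstract poses. Grouping also discards the ordering within each stratum, which matters in a sample of 20 to 30.

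**Working it through.** **1. The plan's own figures.** With p = 0.25 and n = 50, the arcsine interval is sin²(arcsin√0.25 ± 1.96/(2√50)) = sin²(0.5236 ± 0.1386), or 14.1% to 37.8%. The Wilson interval for 12/50 is 14.3% to 37.4%. The stated limits ("for a prevalence of 25% with lower and upper intervals of 14.1% and 37.4% respectively") agree to within about 0.4 points. Power against 10%, arcsine, two-sided 5%: 2(0.5236 − 0.3218)√50 − 1.96 = 0.89, giving 81%, against 80% stated. The prevalence calculation is sound. None is given for the troponin-stratified imaging comparison.

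**2. How likely a shortfall is.** Expected number raised: 50 × 0.25 = 12.5. For X binomial(50, 0.25), P(X ≥ 15) = 0.252 and P(X ≥ 20) = 0.014. So the lower end of the 15–20 target is missed about three times in four, even if every raised patient is imaged. Without enrichment of the imaged subset, 20 × 0.25 = 5 to 30 × 0.25 = 7.5 raised patients would be expected in it.

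**3. Mixing, if strata hold equal numbers.** With n imaged, k raised and two strata, n/2 − k normal patients fall in the high stratum when k < n/2. For n = 30:

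| Raised (k) | Normal in high half | Share of 15 | Normal in top third (of 10) |
|---|---|---|---|
| 5 | 10 | 67% | 5 |
| 7 | 8 | 53% | 3 |
| 8 | 7 | 47% | 2 |
| 12 | 3 | 20% | 0 |

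If imaging values shift by a fixed amount at the 99th centile, the median split retains k/(n/2) of that shift: 8/15 = 53% with 8 raised.

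**4. Power.** The documents give no imaging effect, so two shapes are assumed. *Graded*: log troponin and a continuous imaging value are bivariate normal. *Step*: imaging values rise by 1 SD at the 99th centile and are otherwise unrelated to troponin. Tests are two-sided at 5%: t-tests for groups, Pearson test for continuous troponin. Simulated power, n = 30, 20,000 runs:

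| Shape | Raised | 99th-centile split | Median split | Top v bottom third | Continuous |
|---|---|---|---|---|---|
| Graded, r = 0.5 | 8 | 53.6% | 61.2% | 69.8% | 83.3% |
| Graded, r = 0.5 | 5 | 44.0% | 60.2% | 69.3% | 82.6% |
| Graded, r = 0.4 | 8 | 35.3% | 40.5% | 47.6% | 60.2% |
| Graded, r = 0.4 | 5 | 28.8% | 40.8% | 47.8% | 61.0% |
| Step, 1 SD | 8 | 64.6% | 24.8% | 36.6% | 38.1% |
| Step, 1 SD | 5 | 50.6% | 11.8% | 15.3% | 23.3% |

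A hand check on the continuous column by Fisher's z: atanh(0.5) × √27 − 1.96 = 0.89, or 81%; atanh(0.4) × √27 − 1.96 = 0.24, or 60%. At n = 20 with 5 raised and r = 0.5, the four columns are 35.2%, 42.1%, 49.0% and 64.7%. Continuous troponin has more power than either form of equal strata in every row. The large-sample efficiency of a median split relative to continuous troponin is 2/π = 0.64.

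**5. False-positive rate.** With no association and 5 of 30 raised, each split rejects in about 5% of runs. Keeping whichever split looks better after seeing both results rejects in about 9%.

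**The case against.** The other side has real force on several points.

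- *The fallback may never be used.* The imaged subset is selected, and imaging 12 raised patients with 10 normal ones would give a raised majority, so a median split would put no normal patient in the high half. This stands: mixing is conditional. But the target is qualified as feasible only, and without a stated trigger nobody can tell whether 12 raised patients would count as small.
- *Equal strata of troponin value could mean equal width.* Mixing need not occur then. This stands as a reading. The text does not settle it.
- *The detail may be in a fuller plan.* Possibly for the threshold. The article nevertheless states the rule, and defining the trigger would not remove the mixing or the loss against continuous troponin.
- *The study is exploratory.* True. The association is primary only in the abstract; none of the four primary objectives names it, and no imaging power is claimed. That limits the weight of the point, but the comparison is still to be tested at 0.05.

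Three stronger readings may tempt a reader, and the documents do not support them. First, that the switch gives up power compared with the test it replaces: this holds for a step effect, but for a graded one the median split gains (61% against 54% with 8 raised, r = 0.5). Second, that the cut-point is picked to suit the results: the stated trigger is a troponin count, the Image analysis section blinds readers to blood results, and a switch on counts alone keeps the error rate near 5%. The 9% needs a choice made after seeing both results, which the plan does not propose. Third, that the plan treats age and sex as confounders of the troponin comparison: it tries to match COVID-negative controls on them, which says nothing about confounding among patients.

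**Conclusion.** The point holds in a limited form. The fallback is incompletely specified, and on the plan's own prevalence the shortfall that could set it off is more likely than not (about 75% for fewer than 15 raised of 50). If strata hold equal numbers and the raised group is smaller than the top stratum, the fallback no longer compares injured with uninjured patients. The 7 of 15 is an illustration that assumes 8 raised among 30 and two strata. It is also the weaker use of the data: about 61% power against 83% for continuous troponin at correlation 0.5 and 41% against 60% at 0.4 (bivariate normal, n = 30), and 25% against 38% for a 1-SD step with 8 raised.

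The power figures apply to continuous imaging values only. Several of the plan's findings are present or absent, and the figures do not carry over to them directly. Nor does continuous troponin always win: for a pure step at the 99th centile, the 99th-centile split is best (65% against 38% with 8 raised), so it should not be demoted to a descriptive table.

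**What to change.** Delete the equal-strata sentence and put two fixed analyses in its place:

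1. Report the contrast above against below the 99th centile whatever the count, with its estimate and 95% confidence interval. If few patients are raised, the width of the interval shows it.
2. Add an analysis with log troponin as a continuous predictor in all imaged patients: linear regression or rank correlation for continuous imaging values, and logistic regression or an exact method for presence/absence findings. Where regression is used, report the slope, because choosing patients for imaging by troponin alters a correlation coefficient but not the slope of a correctly specified model.

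The cost is a few sentences in the statistics section and one more analysis, with no new data. The continuous analysis assumes linearity on the log scale, which the rank version relaxes to a monotone relation. It has less power than the 99th-centile contrast if the effect is a pure threshold, and the rank version does not recover that, which is why both are kept.
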